## Introduction

Sepsis, characterised by acute organ dysfunction resulting from a dysregulated host response to infection, is a multifaceted disorder that poses a significant mortality risk among patients in non-coronary intensive care units (ICUs).^1–3^ Despite the advancements in sepsis management over the past decade, the mortality rate still exceeds 30%, reaching up to 60% in cases of septic shock.^4^ In high-income countries, the population incidence rate of sepsis was 437 cases per 100 000 person-years, resulting in approximately 2.8 million deaths attributed to sepsis annually.^5^ Jiang *et al*^6^ reported a standardised sepsis incidence and mortality rate of 461 and 79 cases per 100 000 person-years, respectively, in China. The incidence is expected to rise further due to the ageing Chinese population, leading to an increased financial burden associated with treatment. Consequently, prioritising the management of sepsis and septic shock becomes crucial for ensuring patient safety.

The primary treatment approach for sepsis emphasises timely intervention, which includes removing the source of infection, administering appropriate antibiotics and restoring tissue perfusion through fluid resuscitation and vasoactive drugs.^7–9^ Indeed, sepsis is a syndrome rather than a specific disease, which highlights the importance of implementing adjuvant therapies that target its underlying pathophysiological mechanisms beyond primary treatment. The 2021 guidelines only provide weak recommendations for adjuvant therapies in sepsis management,^10^ such as the use of intravenous corticosteroids. Consequently, there is a pressing need for safe, effective and affordable adjuvant treatments with minimal adverse effects.

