### Evaluation and outcomes

Participants in the study will undergo clinical evaluation and laboratory testing, as outlined in online supplemental table 1. The collected data will include demographic information such as age and gender, disease diagnosis and progression, interventions and prognosis, as well as adverse events (AEs). The disease diagnosis data will encompass primary and concomitant diseases, blood culture results, white blood cell count and liver and kidney biochemistry. Disease progression data will involve baseline severity scores and serum biomarkers, including Sequential Organ Failure Assessment (SOFA) score, Acute Physiology and Chronic Health Evaluation II (APACHE II) score, procalcitonin (PCT), high-sensitivity C-reactive protein (hs-CRP), interleukin 2 (IL-2), IL-4, IL-6, IL-10, tumour necrosis factor-α (TNF-α) and interferon-γ (IFN-γ). Follow-up values on specific days (day 1 (D1), D3, D5, D7) after randomisation will also be recorded, along with the changes from baseline.

10.1136/bmjopen-2023-072897.supp2Supplementary data

Data related to disease intervention will include the requirement and duration of life support measures like mechanical ventilation, vasoactive drugs and continuous renal replacement therapy. Disease prognosis data will encompass 28-day all-cause mortality, ICU mortality, in-hospital mortality, incidence of new-onset acute kidney injury (AKI) after ICU admission, ICU stay and length of hospital stay. Throughout the study, data on organ dysfunction, occurrence of AKI and safety events will be continuously monitored.

The primary efficacy endpoint of the study is 28-day all-cause mortality. The secondary efficacy endpoints are as follows:

ICU mortalityHospital mortalityDuration of ICU and hospital stayIncidence of new AKI in ICUSOFA/APACHE II scores on specific days (D1, D3, D5 and D7) and their changes from baseline (ΔSOFA/ΔApache II)Demand and duration of life support measures (vasopressors, invasive mechanical ventilation and continuous renal replacement therapy).Lactate concentration of arterial blood on specific days (D1, D3, D5 and D7) and their changes from baseline (ΔLAC).Levels of PCT, hs-CRP, IL-2, IL-4, IL-6, IL-10, TNF-α and IFN-γ on specific days (D1, D3, D5, and D7) and their changes from baseline.The detection of levels of IL-2, IL-4, IL-6, IL-10, TNF-α, and IFN-γ is not mandatory if unavailable.

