### Sample size

In this study, the primary efficacy endpoint was the 28-day all-cause mortality rate. A large-scale epidemiological survey conducted in the ICU revealed that the control group had a 38.2% 28-day all-cause mortality rate. In an RCT comparing the LA injection treatment group, the relative risk reduction was approximately 0.33.^38^ The anticipated 28-day all-cause mortality rate for the treatment group was expected to be 22.9% with a one-sided test, using α=0.025 and β=0.2 (power=80%). The threshold value, Δ, was set at 0.

Participants are randomised at a ratio of 1:1, resulting in a calculated sample size of 160 for each group using a superiority test (where a lower rate is considered superior). Taking into account the anticipated dropout rate of around 10%, the sample size was increased to 176 cases in each group.

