### Allocation

In this study, participants who have been diagnosed with sepsis based on the Sepsis-3 criteria are included in the screening process. Those who meet the eligibility criteria will be randomly assigned to either the treatment or control group using a 1:1 allocation. The randomisation will be conducted using a computer-generated block randomisation schedule with a block size of 8, stratified by site. Each block will consist of four patients receiving the LA injection and four patients receiving a placebo. The randomisation method and block size will not be blinded until all data analysis is completed. The investigators involved in the study will not participate in data collection. The randomisation centre, through net verification, will assign the screened patients at each hospital in a random manner.

To ensure the overall quality and integrity of the clinical trial, code breaks should only occur in exceptional circumstances when knowledge of the actual treatment is absolutely necessary for further patient management. Investigators are encouraged to consult with medical advisors if they believe that unblinding is necessary. Any instances of code breaks must be reported, along with the reason, on the corresponding CRF page. It is important to note that unblinding should not automatically result in the discontinuation of the study drug.

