### Statistical analysis

All analyses, including the primary analyses, will be conducted in accordance with the ITT principle. The data will be analysed using R software V.3.3.3 (R Foundation for Statistical Computing, Vienna, Austria) and RStudio V.1.0.136 (RStudio, Boston, MA, USA). Descriptive statistics will be used to describe the data’s distribution, with continuous data presented as mean (SD) or median and IQR, depending on the data characteristics. Categorical data will be reported as number and percentage. Group comparisons will be conducted using group t-tests or analysis of variance for continuous data assuming normality, and non-parametric tests will be used if normality assumptions are not met. Categorical results will be compared using χ^2^ test or Fisher’s exact test. The statistical significance level for all tests will be set at a p value of less than 0.05.

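### The only test named for 28-day mortality is unadjusted: it is valid, but it forgoes efficiency that baseline severity (and, marginally, site) could supply

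*Protocol article*

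**What the plan says.** The endpoint is binary: "The primary efficacy endpoint of the study is 28-day all-cause mortality" (Evaluation and outcomes). Under Statistical analysis the article commits to intention to treat, "All analyses, including the primary analyses, will be conducted in accordance with the ITT principle", and for binary or other categorical outcomes states: "Categorical results will be compared using χ^2^ test or Fisher’s exact test". No stratified, model-based or covariate-adjusted method appears elsewhere in the article. The Sample size section likewise treats the trial as a plain comparison of two proportions.

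Two other sections supply information that this test does not use. Allocation describes a "computer-generated block randomisation schedule with a block size of 8, stratified by site", and Table 1 lists eight hospitals. Evaluation and outcomes says "Disease progression data will involve baseline severity scores and serum biomarkers", and names SOFA and APACHE II among them. Sepsis and septic shock are enrolled together, and the Introduction describes their prognosis thus: "the mortality rate still exceeds 30%, reaching up to 60% in cases of septic shock".

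**The concern.** An analysis normally reflects the factors used to restrict randomisation, and a mortality trial in a mixed sepsis population normally uses a strong baseline severity measure if it has one. The named test pools all sites and ignores severity. Two things are at stake.

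- **Power.** Variation in outcome that baseline severity could explain is left as noise.
- **Chance imbalance.** Shock and severity are not stratification factors, so neither design nor analysis corrects an unlucky split. As a rough illustration, take the Introduction's 30% and 60% as a 30-point gap. An assumed 10-percentage-point imbalance in the share with shock would then move the crude mortality difference by 0.10 × 30 = 3 points, against a planned difference of 38.2 − 22.9 = 15.3 points.

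**Working it through.** **Inputs from the article.** Control mortality is given as "the control group had a 38.2% 28-day all-cause mortality rate", and for the other arm: "The anticipated 28-day all-cause mortality rate for the treatment group was expected to be 22.9% with a one-sided test". Sample size also gives one-sided α = 0.025, 80% power, 1:1 allocation, 160 per arm (176 after a 10% dropout allowance) and a cited relative risk reduction (RRR) of about 0.33. Allocation gives blocks of 8 within site; Table 1 gives eight sites.

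**Step 1. The plan's own sample size.** Pooled formula: n = [z(α)·√(2p̄q̄) + z(β)·√(p1q1 + p2q2)]² / (p1 − p2)².

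- p̄ = 0.3055, √(2p̄q̄) = 0.6514, √(p1q1 + p2q2) = 0.6424.
- n = [1.960 × 0.6514 + 0.8416 × 0.6424]² / 0.153² = 3.303 / 0.02341 = 141.1, so 142 per arm (154 with continuity correction).

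The stated 160 is not reproduced. It is larger than required, so the crude test has power to spare at 22.9%.

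**Step 2. Power of the crude test.** Power = Φ{[(p1 − p2)√n − 1.960·√(2p̄q̄)] / √(p1q1 + p2q2)}.

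- 38.2% vs 22.9%, n = 160: (1.9353 − 1.2767) / 0.6424 = 1.025, giving 84.7%. Fisher's exact test gives 82.0%. At n = 176 the formula gives 87.9%.
- The cited RRR of 0.33 implies 0.382 × 0.67 = 25.6%, whereas 22.9% implies 1 − 0.229/0.382 = 0.40. At 25.6%, n = 160: (1.5946 − 1.2919) / 0.6531 = 0.463, giving 67.8% (Fisher 63.8%). At n = 176 the formula gives 72.0%.

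**Step 3. Gain from adjustment.** Simulation: 4,000 trials per scenario, 160 per arm, eight equal sites, permuted blocks of 8, a logistic outcome model with marginal rates held at the values above, one-sided α = 0.025. The SDs of severity and site on the log-odds scale are assumptions. Site SDs of 0.3 and 0.43 correspond to an ICC of 0.027 and 0.053. Entries are power in %: crude / Mantel-Haenszel by site / logistic with site and severity.

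| Severity SD (AUC) | Site SD | 22.9% | 25.6% |
|---|---|---|---|
| 0 (about 0.50) | 0 | 85.3 / 85.1 / 85.6 | 68.1 / 67.9 / 68.6 |
| 0 (about 0.50) | 0.43 | 85.9 / 86.4 / 86.8 | 69.5 / 70.6 / 71.0 |
| 0.6 (about 0.66) | 0 | 86.3 / 86.3 / 88.6 | 67.4 / 67.2 / 71.1 |
| 0.6 (about 0.66) | 0.3 | 85.1 / 85.2 / 88.6 | 68.9 / 69.5 / 72.7 |
| 0.9 (about 0.72) | 0.3 | 85.6 / 85.8 / 90.9 | 68.4 / 68.7 / 75.3 |
| 1.2 (about 0.77) | 0.3 | 85.1 / 85.1 / 91.5 | 67.0 / 67.2 / 77.2 |
| 1.2 (about 0.77) | 0.43 | 85.9 / 86.2 / 92.2 | 68.4 / 69.2 / 78.3 |

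In the rows with a prognostic score, the adjusted analysis gains 2.3 to 6.4 points at 22.9% and 3.7 to 10.2 at 25.6%. Stratifying by site alone changes power by −0.2 to 1.1 points. With a useless score (first row) adjustment costs nothing visible.

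A second simulation used all 352 patients without dropout (1,200 trials per scenario, severity SD 0.8 to 1.0, site SD 0.4 to 0.6) at 38.2% vs 25.6%. It gave 73% crude, 74 to 75% by site and 78 to 81% adjusted. There site alone added 1.0 to 2.9 points.

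**Step 4. Validity.** With no treatment effect (38.2% in both arms), the crude test in the first simulation rejected in 1.9 to 2.9% of trials and the adjusted model in 2.2 to 3.1%, against a nominal 2.5%. The Monte Carlo standard error is √(0.025 × 0.975 / 4000) = 0.25 points. There is no sign of inflation in the crude test. The lowest figure, 1.9%, occurs with strong site variation, which fits a slightly conservative test.

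**The case against.** The case for leaving the plan alone is substantial.

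- **The crude test is legitimate.** It is valid under 1:1 blocks within site and matches the comparison on which the trial was sized. This stands.
- **Site hardly matters.** The gain from site alone is about 0 to 3 points, and severity, which supplies the rest, was never a randomisation factor. This stands.
- **Planned power is already met.** At 22.9% the crude test exceeds 80%. The shortfall appears only at 25.6%, which comes from a separate inconsistency in the Sample size section, and adjustment does not cure it at 160 per arm. This stands.
- **The gain rests on assumptions.** The documents give neither the prognostic strength of the scores nor the between-site variance. The simulated model also adjusts for the very variable that generated the outcome, with none missing. A noisier score amounts to a lower AUC and a smaller gain. This stands, and is why ranges are shown.
- **The sentence is generic and the analysis plan is unseen.** The words about primary analyses attach to intention to treat, not to the χ² test, and an analysis plan could add an adjusted model. This weakens the point but does not remove it: the article does name a test, and it is the only one that covers the primary endpoint.

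**Conclusion.** The plan names a valid but inefficient primary test. Adjusting for site and one baseline severity score would add roughly 2 to 7 power points at the planned 22.9% and 4 to 10 points at 25.6%, with 160 per arm and an assumed AUC of about 0.66 to 0.77. Nearly all of this comes from severity. It would also reduce exposure to chance imbalance in severity. It is a recommended improvement, not the correction of a mistake.

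Three stronger readings are tempting and are not supported:

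- **That ignoring the stratification makes the result invalid.** The pooled standard error can only be slightly too large, which errs on the cautious side, and the crude test's rejection rate under no effect is not inflated.
- **That the trial lacks power because of this choice.** At its stated rates it does not. At 25.6% it falls short, but because of the assumed effect, and at 160 per arm the adjusted analysis reaches only 71 to 78%. Only with all 352 patients and no dropout do the simulated figures (78 to 81%) straddle 80%.
- **That the plan contradicts itself.** Stratifying the randomisation and then pooling is less efficient, but not contradictory.

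**What to change.** Before any outcome data are seen by arm, pre-specify by documented amendment:

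1. **Primary analysis.** A logistic regression of 28-day death on treatment, site and one named baseline score, either SOFA or APACHE II. Let the treatment coefficient decide the test; that is the test simulated above. Add septic shock at randomisation only if it is recorded or can be derived at baseline. It is not listed as a collected variable, although the entry diagnosis may supply it.
2. **Reporting.** A standardised risk difference and risk ratio with 95% confidence intervals, so that the effect stays on the scale used for sample size.
3. **Supportive analysis.** The crude χ² or Fisher test.
4. **Practical rules.** How a missing baseline score and a very small site are handled, so that every randomised patient is kept.

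The model is affordable. Expected deaths are about 176 × (0.382 + 0.229) = 108, for nine terms (treatment, seven for site, one score), or ten with shock.

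The cost is an amendment and slightly more analysis work; both scores are already collected. Timing matters because recruitment began in August 2021 and the trial is single-blind, so covariates chosen late could look data-driven.

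### An unadjusted p<0.05 for every test lets each of up to 99 secondary comparisons be declared significant on its own

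*Protocol article*

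**What the plan says.** All references are to the protocol article.

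- **Statistical analysis** gives the only significance rule: "The statistical significance level for all tests will be set at a p value of less than 0.05". It does not say whether p-values are one- or two-sided. For binary outcomes it adds: "Categorical results will be compared using χ^2^ test or Fisher’s exact test".
- **Sample size** gives the only statement of direction. The trial is sized on 28-day mortality "with a one-sided test, using α=0.025 and β=0.2 (power=80"%), and "The threshold value, Δ, was set at 0".
- **Evaluation and outcomes** names one primary endpoint, 28-day all-cause mortality. The secondary efficacy endpoints are ICU and hospital mortality, ICU and hospital stay, new acute kidney injury (AKI), need for and duration of three kinds of life support, SOFA and APACHE II, arterial lactate, and eight blood markers: "Levels of PCT, hs-CRP, IL-2, IL-4, IL-6, IL-10, TNF-α and IFN-γ on specific days". The scores, lactate and markers are each listed on four days and again as changes from baseline. Six of the eight markers, the cytokines, need not be measured where the assay is unavailable.
- **Interim analysis** schedules none.

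The article gives no order of testing, no multiplicity adjustment and no exploratory label for the secondary endpoints.

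**The concern.** The article does more than leave multiplicity open. It sets a level and extends it to every test. Under that rule a lower IL-6 on day 3 with p=0.04 is as significant as a mortality difference with p=0.04.

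This matters because the Introduction sets out to show effects on inflammation, organ dysfunction, length of stay and mortality, and the Discussion expects the trial to support recommendations. If mortality turns out neutral, a few low p-values on scattered marker days could be presented as efficacy while following the stated rule to the letter. With this many comparisons, some low p-values are expected from an inert treatment.

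A smaller point sits in the same sentence. The reader has to supply the sidedness of 0.05, because the only direction given in the article is the one-sided test in the Sample size section.

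**Working it through.** **1. Does 0.05 agree with the design level?**

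Critical values:
- one-sided 0.025: z = 1.960
- two-sided 0.05: z = 1.960
- one-sided 0.05: z = 1.645

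The first two give the same boundary for benefit. The sample-size formula confirms this. The inputs are control 38.2% ("the control group had a 38.2% 28-day all-cause mortality rate") and LA 22.9% ("The anticipated 28-day all-cause mortality rate for the treatment group was expected to be 22.9"%), with 80% power:

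n = [z_α·√(2·p̄·(1−p̄)) + z_β·√(p₁(1−p₁)+p₂(1−p₂))]² / (p₁−p₂)²

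with p̄ = (0.382+0.229)/2 = 0.3055.

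- z_α = 1.960: [1.960×0.6514 + 0.8416×0.6424]² / 0.153² = 141.1, so 142 per group, whether written as one-sided 0.025 or two-sided 0.05. Power at 160 per group is 84.7% either way.
- z_α = 1.645: 112 per group, and power at 160 is 91.1%.

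The stated 160 per group is not reproduced (142, or 154 with continuity correction). That is a separate matter and does not bear on this point.

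**2. Would the missing word ever change the result?**

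Only if 0.05 were applied to a one-sided p-value. A made-up example with 176 per group: 67 control deaths (38.1%) and 51 LA deaths (29.0%).

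- Pooled proportion: 118/352 = 0.335
- Standard error: √(0.335×0.665×2/176) = 0.0503
- z = 0.0909/0.0503 = 1.81
- One-sided p = 0.035; two-sided p = 0.071

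The two-sided p fails at 0.05 and the one-sided p fails at 0.025, so those two readings agree. Only a one-sided p held against 0.05 would pass.

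**3. Count of secondary comparisons**

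The article gives no count. This one is taken from the endpoint list in Evaluation and outcomes.

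| Endpoint | Arithmetic | Comparisons |
|---|---|---|
| ICU mortality, hospital mortality | 1+1 | 2 |
| ICU stay, hospital stay | 1+1 | 2 |
| New AKI | 1 | 1 |
| Life support: 3 measures, demand and duration | 3×2 | 6 |
| SOFA and APACHE II: 4 days, level and change | 2×4×2 | 16 |
| Lactate: 4 days, level and change | 4×2 | 8 |
| Eight markers: 4 days, level and change | 8×4×2 | 64 |
| **Total** | | **99** |

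The six optional cytokines account for 6×4×2 = 48, so 99−48 = 51 remain without them.

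**4. Expected false positives if LA has no effect**

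Expected number = m × 0.05. With two-sided tests, about m × 0.025 favour LA.

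| Comparisons m | Expected p<0.05 | Of these favouring LA | P(at least one) if independent, 1−0.95^m |
|---|---|---|---|
| 99 | 4.95 | 2.5 | 99.4% |
| 51 | 2.55 | 1.3 | 92.7% |

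The expected numbers do not need independence. The last column does, and because levels, changes and successive days are correlated it is only an upper guide. If level and change are counted once, 5+8+6+4+32 = 55 comparisons remain, with 2.75 expected.

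**The case against.** **Multiplicity belongs to the analysis plan.** Hierarchies and adjustments for secondary endpoints are commonly left to a statistical analysis plan, which is not shown here, and silence in an article would be no finding. That is right as a principle, but this article is not silent. It fixes 0.05 for every test, and a plan with a hierarchy or exploratory labels would have to depart from that sentence.

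**The count of 99 is a ceiling.** This stands. The article lists what will be measured and does not say that each day, level and change gets its own test. Nearly half the comparisons (48 of 99) depend on assays that centres may not have. Hence the range from 51 to 99, and the note that only about half of the false positives would favour LA.

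**The primary endpoint is protected.** This also stands. There is one primary endpoint and no interim look, so the number of secondary tests does not change its error rate. The article nowhere says that a secondary result alone would establish efficacy.

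**A stronger reading that the text does not support.** A reader might set the one-sided 0.025 of the Sample size section beside the 0.05 of the Statistical analysis section and infer a contradiction that doubles the false-positive rate for mortality from 2.5% to 5%. That requires 0.05 to be applied to a one-sided p-value, which the article does not say. The χ² test it names is non-directional, so p<0.05 means |z|>1.960, the same boundary for benefit as in the design. Fisher's exact test can be run one-sided, so the test names do not settle the matter completely, but it is normally run two-sided. What is missing is the word two-sided.

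**Conclusion.** The point holds for the secondary endpoints. The stated rule allows each of 51 to 99 comparisons to be declared significant at an unadjusted 0.05, with about 2.6 to 5 false positives expected under no effect, roughly half of them (1.3 to 2.5) in LA's favour. These figures assume that each score and marker is tested on each of the four days as both level and change, and that each test has its nominal size. The lower figure assumes that no optional cytokine is measured.

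The primary endpoint's type I error is unaffected. The design level and the analysis level agree when the p-value is two-sided, so a claim of conflicting thresholds or a doubled error rate for mortality should not be made. The unstated sidedness needs a clarification only. The whole point concerns how results may be claimed, and it does not touch the validity of the mortality comparison.

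**What to change.** In the Statistical analysis section, replace the blanket rule with statements to this effect:

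1. The primary endpoint is tested two-sided at 0.05, which is equivalent for benefit to the one-sided 0.025 used for the sample size.
2. Claims of statistical significance are limited to the primary endpoint. Secondary endpoints are reported as between-group estimates with 95% confidence intervals and labelled exploratory.

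No endpoint needs to be added or dropped. The cost is fewer secondary significance claims. Sample size, power and trial conduct stay as they are, because both ways of writing the primary level share the critical value 1.960.
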